### Study participants and eligibility criteria

2.2

#### Inclusion criteria

2.2.1

To be eligible for participation in this study, potential participants must be adult females or males aged 18 to 65 years inclusive and be treated as in- and/or outpatients. Participants must have a primary diagnosis of MDD, of moderate or severe severity according to DSM-5 criteria. They need to agree to start a new bout of allopathic or Ayurvedic treatment in the current episode regardless of any previous treatments received during the current episode. They must provide informed consent to participate. They must also be willing to fully participate and adhere to the study protocol.

#### Exclusion criteria

2.2.2

Individuals will be excluded from participation in this study if they have a current diagnosis of any severe psychiatric disorder other than MDD, such as bipolar disorder or schizophrenia. Participants with active suicidal ideation or behaviour , as assessed by the Columbia-Suicide Severity Rating Scale (C-SSRS) with a score of 4 or higher and with a moderate or severe alcohol use disorder within the past 12 months or any current alcohol or drug use disorder will be excluded. Pregnant or breastfeeding individuals will be excluded from the study to protect both the mother’s and the foetus ‘/infant’s health. Participants with significant medical or neurological conditions that could interfere with their ability to participate in the study or that may confound the interpretation of the results will be excluded. Participants who have significant language barriers that may hinder their understanding of study procedures or their ability to provide informed consent will be excluded.

### Study intervention

2.3

This study will utilize a naturalistic observational design, leveraging the established expertise and practices of two distinct clinical settings: Nadiad Ayurveda Hospital (for Ayurvedic only and combined treatments) and Shree Krishna Hospital, Department of Psychiatry, Bhaikaka University, Karamsad, Anand (for allopathic treatments). The assignment to the groups follows a clear system. The two hospitals have different areas of focus. One clinic (Shree Krishna Hospital) provides exclusively allopathic treatment, while the other (Nadiad Ayurveda Hospital) provides Ayurvedic treatment. Patients who are treated at the Ayurvedic hospital but have previously received allopathic treatment will continue to receive allopathic treatment (combined therapy). The clinic is selected based on clinical indications and in consultation with the patient.

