Ayurvedic medicine, an ancient holistic system originating from India, offers an alternative and complementary approach to MDD (10). This system emphasizes the interconnectedness of mind, body, and spirit, aiming to restore balance through various interventions. These include herbal remedies (e.g., Ashwagandha, Brahmi etc.), dietary modifications tailored to individual constitution (Prakriti), lifestyle adjustments promoting holistic well-being, and mind-body techniques such as yoga and meditation (11). Ayurvedic treatment is well established in India. It is a holistic whole system approach that traditionally consists of specific components (Panchakarma, manual therapies Dietary Modifications, Herbal Formulations, Lifestyle Modifications, Sattvavajaya and Daiva-vyapasraya-cikitsa) that are integrated into a common treatment approach. There are special hospitals that specialize in such holistic treatment concepts. Patients can choose whether they want to be treated in an allopathic or an Ayurvedic hospital. While level A (e.g. meta-analysis and RCTs) and level B (evidence from at least one high-quality study or multiple moderate-quality studies) evidence studies and some smaller studies suggest the potential efficacy of Ayurvedic treatments in alleviating depressive symptoms (12–14), robust, large-scale randomized controlled trials comparing Ayurvedic treatment to allopathic treatments are relatively scarce (15). Understanding the mechanisms through which Ayurvedic treatment exert their effects on mood and related symptoms remains an area of active research.

This necessitates a more comprehensive understanding of the relative treatment effects, side effects and potential synergistic effects of integrating allopathic and Ayurvedic treatments for MDD. A comparative evaluation of these approaches is crucial for informing evidence-based clinical practice and optimizing therapeutic strategies for individuals experiencing this pervasive and debilitating disorder. This study aims to address this critical gap in the literature through observation and analysis of real-world outcomes of allopathic and ayurvedic treatment modalities for MDD.

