**Figure 1 f1:**
[figure not shown]
Flowchart of the study visits over time.

Arm A: Allopathic-Only Treatment: Participants in this arm will receive standard allopathic care, including antidepressant medication and psychotherapy as determined clinically appropriate.Arm B: Ayurvedic-Only Treatment: Participants in this arm will receive treatment exclusively with ayurvedic modalities.Arm C: Combination Treatment: This arm permits the integration of both ayurvedic and allopathic treatments, reflecting the increasing trend toward integrated care approaches.

At week 8 participants will be given the opportunity to reevaluate their treatment. This allows for a more patient-centred approach and accommodates individual responses to treatment. This enhances the study’s relevance to real-world clinical practice , where treatment decisions often involve adaptations based on ongoing assessment.

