#### Arm C: combination treatment arm

2.3.3

Patients who are treated at the Ayurvedic hospital but have previously received allopathic treatment will continue to receive allopathic treatment and start new ayurvedic treatment. This arm integrates Allopathic and Ayurvedic treatments, collaboratively managed by both a Psychiatrist and an Ayurvedic specialist. The treatment strategy will be individualized, considering both the patient’s clinical presentation and preferences.

A patient who is already on Allopathic medication (antidepressants) from their psychiatrist and wishes to start ayurvedic treatment would be categorized into this group. The Ayurvedic specialist and the patients treating Psychiatrist would collaboratively decide whether to maintain, reduce, or discontinue the Allopathic medication as the Ayurvedic treatment progresses. If no Allopathic treatment has been initiated, Ayurvedic treatment will be administered for eight weeks before a joint clinical decision is made regarding the addition of allopathic medication. This approach aims to leverage the potential synergistic effects of both treatment modalities, promoting personalized and effective management of MDD. Previous studies have shown that allopathic psychiatric medication can be combined safely with Ayurvedic treatments such as herbs (10, 11, 16–18).

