### Study assessments

2.4

All three arms will involve structured assessments at baseline, every 2 weeks until week 8, followed by monthly assessments up to month 6 to measure symptom severity, quality of life, functional capacity, adverse events, and adherence (see **figure 2** for a detailed overview of assessment schedules across all visits). The study will involve a detailed medical history, including sociodemographics, medical and psychiatric history, and previous and current medication. Clinical symptoms related to depression, trauma, and sleep are assessed using the test procedures described below.

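### Earlier allopathic treatment decides Arm B versus Arm C but is unrestricted in Arm A, and the sorting rule is inconsistent, so every between-arm contrast is confounded with treatment history

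*Protocol article*

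**What the plan says.** Allocation is not randomised. Section 2.3 gives Arm A to the allopathic hospital and Arms B and C to the Ayurvedic hospital, and adds: "The clinic is selected based on clinical indications and in consultation with the patient".

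At the Ayurvedic hospital the divide is treatment history: "Patients who are treated at the Ayurvedic hospital but have previously received allopathic treatment will continue to receive allopathic treatment (combined therapy". Section 2.3.3 opens by repeating this, then states a different criterion: "A patient who is already on Allopathic medication (antidepressants) from their psychiatrist and wishes to start ayurvedic treatment would be categorized into this group". A third sentence under the same arm covers the opposite case: "If no Allopathic treatment has been initiated, Ayurvedic treatment will be administered for eight weeks before a joint clinical decision is made". Arm B is described in section 2.1: "Participants in this arm will receive treatment exclusively with ayurvedic modalities".

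For eligibility, section 2.2.1 accepts patients who start a new bout of either treatment "regardless of any previous treatments received during the current episode".

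The first objective (section 1.2) is to compare the allopathic, Ayurvedic and combined treatments on depressive symptoms. Section 2.7 puts the emphasis on week 8. Section 2.9 corrects for confounders only where the groups differ significantly and names none. Section 3.2 concedes confounding and selection bias in general terms. Section 2.4 collects "medical and psychiatric history, and previous and current medication".

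**The concern.** A declared observational study may have unbalanced arms. This imbalance, however, is written into the arm definitions. At one hospital, earlier allopathic treatment decides the arm; at the other it plays no part. A between-arm difference at week 8, or its absence, may then reflect who was eligible for each arm and not what they received. Because sections 1.2 and 2.9 predict no between-group difference, a real difference masked by this selection would look like confirmation.

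Two further things are at stake. First, who belongs in which arm is not fixed, because the criteria disagree. Second, change from baseline does not mean the same thing throughout. For a patient already on an antidepressant, only the Ayurvedic part is new at baseline, so Arm C measures what follows its addition. The rationale in section 1.1 nevertheless speaks of "potential synergistic effects of integrating allopathic and Ayurvedic treatments for MDD".

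**Working it through.** **1. Trace the rules by allopathic treatment status at entry.**

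| Status at entry | Allopathic hospital | Ayurvedic hospital, by past receipt (2.3, opening of 2.3.3) | Ayurvedic hospital, by the later text of 2.3.3 |
|---|---|---|---|
| None | A | B, by remainder | described under C; Ayurvedic treatment alone for eight weeks |
| Stopped before entry | A | C | not placed by the current-use criterion |
| Current | A | C | C |

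Only the last row is unambiguous. In the middle row, the instruction to continue allopathic treatment does not fit someone who has stopped it. In the first row, an untreated patient counted in Arm C has the same type of treatment up to week 8 as a patient in Arm B.

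B versus C is the only contrast within one hospital, and history defines it. A versus B and A versus C can be stratified by history to the extent that Arm A is mixed, but they coincide with hospital. No contrast is free of both.

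**2. The plan's own figure.** Section 2.9 claims power above 0.8 for effect size 0.5 and N = 105. Assuming two-sided alpha 0.05, a paired t-test in one arm of 35 gives 0.82, so the claim holds for the within-group question. The between-arm comparison, 35 v 35 at 0.5 SD, has power 0.55 (normal approximation). The present point does not depend on this figure; 0.55 is the reference for step 4.

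**3. What the imbalance could do, unadjusted.** The documents give no pretreated shares and no history effect, so these are assumptions. With no true treatment difference, bias = (difference in pretreated share) × (history effect in SD). The standard error in SD units is √(2/35) = 0.239. The rejection rate of a nominal 5% two-sided z-test is 1 − Φ(1.96 − bias/0.239) + Φ(−1.96 − bias/0.239).

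| History effect | Shares differ by 100 points | Shares differ by 50 points |
|---|---|---|
| 0.2 SD | 13% | 7% |
| 0.3 SD | 24% | 10% |
| 0.5 SD | 55% | 18% |

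These rates apply whichever arm is favoured.

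**4. What adjustment within B versus C can recover.** Suppose nobody in B and a share q of C is pretreated. The squared correlation between arm and history is q/(2 − q), so the variance inflation is (2 − q)/(2(1 − q)).

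- q = 1: infinite. The contrast cannot be adjusted.
- q = 0.8: 1.2/0.4 = 3.0. Effective n per arm 35/3.0 = 11.7; power for 0.5 SD falls from 0.55 to 0.23.
- q about 0.5 (18 of 35): 1.53. Effective n 22.9; power 0.39.

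In a three-arm model with q = 1, the history coefficient comes from Arm A alone. An adjusted B versus C then assumes that history acts the same way at both hospitals.

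**5. Cost of splitting Arm A.** With m Arm A patients in the relevant stratum, the standard error relative to 35 v 35 is √[(1/35 + 1/m)/(2/35)]. The SD cancels from the ratio; SD 10 is assumed only to show points.

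- Unsplit: 10√(2/35) = 2.39.
- Half of Arm A pretreated, m = 17.5: 10√(1/35 + 1/17.5) = 2.93, up 22% (either contrast).
- 30% pretreated, C versus pretreated A, m = 10.5: 10√(1/35 + 1/10.5) = 3.52, up 47%.
- 60% pretreated, B versus untreated A, m = 14: 10√(1/35 + 1/14) = 3.16, up 32%.

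**The case against.** The study is openly non-randomised, exploratory and hypothesis-generating (sections 1.2, 2.1 and 4). It admits confounding and preference-driven choice (3.2), plans a correction (2.9) and records medication history (2.4). Its hypothesis of improvement is within-group. All this stands and lowers the severity. It does not settle the point: section 3.2 does not name the sorting rule, and the correction in 2.9 would very likely be triggered at full separation, exactly where it cannot work within B versus C.

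A reader might also infer more than the text supports:

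- *Arm C is made up of insufficient responders.* Section 2.3.3 also describes patients with no allopathic treatment under Arm C. No minimum duration, dose or failed course is required, so someone who began an antidepressant shortly before entry qualifies, and much of that response could fall after baseline.
- *Arm B is favoured and Arm C handicapped.* For the same reason the direction is open, and the effect of clinical indication on the choice of hospital is unknown.
- *Arm B excludes everyone treated earlier.* If only current users belong in Arm C, Arm B could hold patients who stopped.
- *The arms are at different stages of illness.* The rule sorts by treatment history; the article gives no data on stage or episode duration by arm.
- *The 30% resistance figure in section 3 sizes the bias.* It describes treated cases in general, neither the mix in Arm A nor a difference in MADRS change.
- *Synergy is a trial objective.* It appears in the rationale (1.1) and the description of Arm C (2.3.3), but is not among the three objectives in 1.2.

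**Conclusion.** The point holds as a structural confounding and definition problem. Earlier allopathic treatment determines B versus C and is unrestricted in A, so all three contrasts carry it. If B and C do not overlap on it, their contrast cannot be adjusted from its own data. The arm definitions conflict over patients who stopped allopathic treatment and over those who never started it.

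The size is not known from the documents. The illustrations (false rejection 13% to 55% at full separation, 7% to 18% at half) rest on assumed history effects of 0.2 to 0.5 SD. The mix in Arm A follows from the entry criterion, but its share is unstated.

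This should be fixed. It is not fatal, because the design is declared exploratory and the within-group question does not depend on it.

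**What to change.** 1. Reconcile sections 2.3 and 2.3.3 into one arm definition based on allopathic treatment status at baseline in the current episode: none, stopped or current. State where each status is counted, including untreated patients described under Arm C. This concerns classification only; which patients continue, stop or start a treatment is for the sponsor to reconcile.
2. Put that status into the between-arm model as a prespecified covariate, whether or not it differs significantly, in place of the significance-triggered rule in section 2.9.
3. Report B versus untreated Arm A and C versus pretreated Arm A as supporting contrasts. Say that the latter compares adding Ayurvedic care to existing treatment with starting a new allopathic bout; it is not combination against continued allopathic treatment.
4. State that, for patients already on antidepressants, Arm C estimates the change after adding Ayurvedic care to existing allopathic treatment, and that B versus C or A versus C is not evidence for or against synergy.
5. State that A versus B and A versus C remain confounded with hospital.

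The cost is mainly wording. Medication history is already collected, but section 2.4 does not say that it covers stop dates or links treatment to the current episode, so the case report form needs checking. The stratified contrasts lose precision: the standard error rises about 22% if half of Arm A is pretreated, and up to about 47% for the pretreated contrast at 30%. They should therefore remain supporting analyses.

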#### Arm A: allopathic treatment arm

2.3.1

Participants assigned to the allopathic treatment arm will receive a comprehensive treatment plan developed and overseen by a licensed psychiatrist. This plan will adhere to current clinical practice guidelines for MDD and will include Pharmacological Intervention, Psychotherapy and Supportive Care.

A standard antidepressant medication regimen will be prescribed. The choice of antidepressant will be guided by evidence-based practice guidelines (Maudsley Prescribing Guidelines and Indian Psychiatric Society guidelines). Dosage adjustments will be made as needed based on clinical response and tolerability. Participants will also receive evidence-based psychotherapy, typically Cognitive Behavioural Therapy (CBT) or Interpersonal Psychotherapy (IPT), guided by a licensed mental health professional. The type and frequency of psychotherapy sessions will be tailored to each participant’s specific needs and clinical presentation.

Participants will receive supportive care as needed, which may include regular monitoring of their mental and physical health, strategies to enhance treatment adherence, and resources to address any practical or social challenges they may be facing.

#### Arm B: ayurvedic treatment arm

2.3.2

Participants in the Ayurvedic treatment arm will receive an individualized treatment plan developed and overseen by a qualified Ayurvedic specialist. Treatment will be individualized, considering each patient’s unique constitution (Prakriti) and the imbalances (Vikriti) contributing to their MDD. This will involve a comprehensive assessment of physical and psychological symptoms, using traditional Ayurvedic diagnostic methods. This plan will be customized to each participant’s unique constitution (Prakriti) and will encompass Panchakarma, manual therapies Dietary Modifications, Herbal Formulations, Lifestyle Modifications, Sattvavajaya and Daiva-vyapasraya-cikitsa.

Depending on the individual’s need and condition, Panchakarma and manual therapies may include Vamana, Virecena, Bastis, Nasya, Shirodhara, Abhyanga, or other suitable treatments as determined by the Ayurvedic specialist. This will be administered by qualified Ayurvedic practitioners following standard Ayurvedic protocols and safety guidelines. Participants will receive personalized dietary advice aimed at promoting balance and well-being. The dietary recommendations will be tailored to their Prakriti and may involve specific food restrictions or recommendations depending upon their individual requirements and constitution. Participants may receive herbal formulations (e.g., Ashwagandha, Brahmi, Jatamansi, Tagara, Kapikacchu) selected based on their individual Prakriti and clinical presentation. The dosage and specific formulation will be determined by the Ayurvedic specialist. The herbal preparations will be sourced from reputable suppliers to ensure quality and purity. Lifestyle recommendations will be integrated into the treatment plan, emphasizing routines and practices that promote mental and physical health. This may include recommendations regarding sleep hygiene, stress management techniques, exercise regimes and the establishment of healthy daily habits. Participants may be recommended to incorporate Sattvavajaya and Daiva-vyapasraya-cikitsa into their daily routines. This may involve specific asanas and pranayama techniques, guided meditation practices, or other mind regulating interventions that support relaxation, stress reduction, and improved mental well-being.

#### Arm C: combination treatment arm

2.3.3

Patients who are treated at the Ayurvedic hospital but have previously received allopathic treatment will continue to receive allopathic treatment and start new ayurvedic treatment. This arm integrates Allopathic and Ayurvedic treatments, collaboratively managed by both a Psychiatrist and an Ayurvedic specialist. The treatment strategy will be individualized, considering both the patient’s clinical presentation and preferences.

A patient who is already on Allopathic medication (antidepressants) from their psychiatrist and wishes to start ayurvedic treatment would be categorized into this group. The Ayurvedic specialist and the patients treating Psychiatrist would collaboratively decide whether to maintain, reduce, or discontinue the Allopathic medication as the Ayurvedic treatment progresses. If no Allopathic treatment has been initiated, Ayurvedic treatment will be administered for eight weeks before a joint clinical decision is made regarding the addition of allopathic medication. This approach aims to leverage the potential synergistic effects of both treatment modalities, promoting personalized and effective management of MDD. Previous studies have shown that allopathic psychiatric medication can be combined safely with Ayurvedic treatments such as herbs (10, 11, 16–18).

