### Trial design and study setting

2.1

This study employs a naturalistic observational (non-randomization) design, conducted within real-world clinical settings for a six-month period (see **Figure 1**) where the group assignment reflects patient preference and clinical practice in specialized hospitals. The study population comprises 105 adult participants. Participants will be observed in one of three treatment groups, each consisting of approximately 35 individuals, based on the treatment they receive (see **Figure 1**).

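### Arm C's section contains an Ayurveda-alone pathway to week 8 that does not fit Arm C's entry rule and leaves the arm of those patients unclear

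*Protocol article*

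**What the plan says.** All places are in the protocol article.

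- **Arm C entry, Section 2.3:** "Patients who are treated at the Ayurvedic hospital but have previously received allopathic treatment will continue to receive allopathic treatment (combined therapy".
- **Arm C entry, Section 2.3.3:** "A patient who is already on Allopathic medication (antidepressants) from their psychiatrist and wishes to start ayurvedic treatment would be categorized into this group".
- **The pathway at issue, also in Section 2.3.3:** "If no Allopathic treatment has been initiated, Ayurvedic treatment will be administered for eight weeks before a joint clinical decision is made" about adding allopathic medication. The sentence after it reads "This approach aims to leverage the potential synergistic effects of both treatment modalities".
- **Arm B, Section 2.1 (arm list below Figure 1):** "Participants in this arm will receive treatment exclusively with ayurvedic modalities".
- **Basis of grouping, Section 2.1:** three groups, "each consisting of approximately 35 individuals, based on the treatment they receive".
- **Week 8, Section 2.1:** "At week 8 participants will be given the opportunity to reevaluate their treatment".
- **Endpoint and analysis:** Section 2.7 puts the emphasis of the primary endpoint on week 8. Section 2.9 states an intention-to-treat, exploratory analysis and hypothesises that the groups do not differ.

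**The concern.** Both statements of Arm C's entry rule require allopathic treatment that is already in place. The pathway sentence deals with patients who have none, yet it stands in the Arm C section and leads into a statement about combining both modalities. A site that follows the section as printed could enter these patients in Arm C.

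This matters more here than it would in a randomised trial. There is no allocation record to fall back on, so the classification rule alone defines the groups. The Ayurveda-alone period also fills the whole interval to the main time point. Patients labelled as combination but treated as Arm B would make B and C look more alike at week 8, which is the direction of the stated hypothesis. Part of a finding of no difference could then come from labelling.

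**Working it through.** **Step 1. Set the rules side by side for one patient.** Take a patient at the Ayurvedic hospital with no allopathic treatment.

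| Rule | Where it points |
|---|---|
| Section 2.3, previous allopathic treatment continues | Not Arm C |
| Section 2.3.3, already on antidepressants | Not Arm C |
| Section 2.1, definition of Arm B | Arm B up to week 8 |
| Section 2.1, grouping by treatment received | Arm B up to week 8; could be read as Arm C once medication is added |
| Section 2.3.3, pathway sentence and the one after it | Can be read as Arm C |
| Section 2.3.2, Arm B's own section | No such pathway, and no joint management with a psychiatrist |
| Section 2.9, intention to treat | Weighs against moving patients between arms later; does not say which arm they enter |

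Most of these rules point to Arm B and one can be read as Arm C. None states the arm at entry, or after an addition at week 8.

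**Step 2. Size the effect of counting them in Arm C.** The plan gives no figure to reproduce here. From the document: 35 per arm. Assumed: k Ayurveda-only patients in Arm C, a true B-C difference of d (in SD units), a two-sided test at 0.05, and Arm B's expected outcome for the k patients.

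With q = k/35, the observed difference is d × (1 − q). For example, k = 7 gives q = 0.20, and 0.5 × 0.80 = 0.40. With d = 0 the result stays 0 at any q.

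Power is from the noncentral t distribution with 68 degrees of freedom. Its noncentrality is the observed difference divided by the standard error. At 35/35 the standard error is √(1/35 + 1/35) = 0.239 SD. In the last two columns the same k patients are counted in Arm B, so the difference is undiluted and the groups are unequal.

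| k | q | Observed, d = 0.3 | Observed, d = 0.5 | Power, d = 0.5, counted in C (35/35) | B/C sizes if counted in B | Power, d = 0.5, counted in B |
|---|---|---|---|---|---|---|
| 0 | 0% | 0.300 | 0.500 | 0.541 | 35/35 | 0.541 |
| 4 | 11% | 0.266 | 0.443 | 0.447 | 39/31 | 0.535 |
| 7 | 20% | 0.240 | 0.400 | 0.378 | 42/28 | 0.524 |
| 11 | 31% | 0.206 | 0.343 | 0.293 | 46/24 | 0.499 |

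A simulation of 40,000 runs at k = 7 and d = 0.5 agrees. It gives a mean difference of 0.40 and power of 0.37 when the patients are counted in C, and 0.50 and 0.53 when they are counted in B.

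**Step 3. Read the result.** The cost of correct labels is only the unequal split, which is small. The cost of the wrong labels is a biased contrast as well as lower power.

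**The case against.** The best case for the text is that it already places these patients. A patient at the Ayurvedic hospital with no allopathic treatment fails both forms of Arm C's rule and meets Arm B's definition, and no other arm fits. The pathway sentence contains no word of assignment, unlike the sentence on patients already taking antidepressants. It only says when adding medication is considered, and its eight weeks match the week-8 re-evaluation. The synergy sentence may refer to the arm as a whole, since eight weeks of Ayurveda alone cannot combine anything. Figure 1, cited where the groups are introduced, is not shown, and the article condenses a fuller protocol.

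Much of this stands. A misplaced management rule is a plausible reading, and the sentence does not expressly assign anyone to Arm C. But Arm B's section has no such pathway, joint management by a psychiatrist and an Ayurvedic specialist is described only for Arm C, and the arm after a week-8 addition is not stated on either reading. Nor is this detail that an article leaves out: the article sets the arm rule itself, and its parts do not agree.

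The points about harm also stand, and they limit how serious this is. The numbers of patients and the differences used above are assumptions. The study is exploratory, and its authors expect no difference between groups. B and C already differ by prior allopathic treatment, and the contrast is weak even with correct labels.

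**Conclusion.** The concern holds: the arm rule is stated inconsistently and should be fixed. It is a limited problem. On the assumed range, misplacing 4 to 11 of 35 patients removes 11% to 31% of any true week-8 difference between B and C. That rests on three conditions: such patients are enrolled, sites count them in Arm C, and they have Arm B's expected outcome. If the true difference is zero, or if sites treat the sentence as an Arm B rule, there is no dilution. Comparisons of A with B are unaffected if these patients are placed in C, apart from Arm B being smaller. Arm A's own membership is not in question. Confidence is medium because the innocent reading of the sentence is a real possibility.

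**What to change.** 1. Set the analysis arm once, at baseline, from data that Section 2.4 already collects ("medical and psychiatric history, and previous and current medication"). At the Ayurvedic hospital, patients on allopathic treatment at baseline are Arm C and those with none are Arm B.
2. Keep patients in that arm under the stated intention-to-treat approach, whatever is added later. Record the date of each addition, reduction or withdrawal of allopathic medication.
3. Move the pathway sentence to Section 2.3.2, or reword it as a rule for management after week 8 that does not change the arm.

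The cost is one sentence moved or reworded and one added, with no new data. B and C may end up unequal: at 42/28 the standard error is √(1/42 + 1/28) = 0.244 SD against 0.239 SD, about 2% more. Arm C may fill more slowly. At months 3 and 6 Arm B will include patients who have added allopathic medication, so their number should be reported.
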